### Separation of auditory-evoked responses from ongoing *δ*-wave activity

3.2

To dissociate auditory event-related potentials (ERPs) from modulation of ongoing δ-wave activity, we will adopt an approach previously validated in CLAS studies during sleep (Ngo et al., 2013). For each stimulation condition, EEG activity time-locked to auditory stimulus onset will be averaged, and the corresponding average from the *sham* condition will be subtracted to isolate stimulus-evoked responses. This procedure allows identification of early auditory ERP components while minimizing contamination from ongoing spontaneous slow oscillatory activity.

Importantly, primary analyses of δ-wave dynamics are based on individually detected δ-waves defined independently of stimulus-locked averaging. δ-wave detection and morphological metrics (amplitude, slope, transition frequency, density) are computed on continuous EEG signals using zero-crossing based criteria, ensuring that reported CLAS effects reflect modulation of endogenous oscillatory activity rather than purely evoked auditory responses.

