### Closed-loop auditory stimulation as a modulator of delta waves

1.5

SWA plays critical roles in sleep physiology, including memory consolidation, metabolic clearance, and the dissipation of homeostatic sleep pressure (Fultz et al., 2019; Krueger et al., 2016). Declines in SWA are consistently linked to aging and neuropsychiatric disorders such as depression, schizophrenia, and dementia (Baglioni et al., 2016; Scullin, 2013). Over the past decade, closed-loop auditory stimulation (CLAS) has emerged as a powerful method to modulate SWA in real time. By delivering auditory stimuli phase-locked to ongoing SOs, CLAS can selectively enhance their amplitude and slope when applied on the ascending phase of SOs, right before the positive peak (called “*in-phase*” or “*peak*” stimulation; Ngo et al., 2013; Ngo et al., 2015). Conversely, stimulation during the descending phase, after the positive peak but before the negative peak (called “*anti-phase*” or “*trough stimulation*”) tends to disrupt SWA expression (Navarrete et al., 2020; Ngo et al., 2013). Thus, the precise timing of auditory stimulation is crucial: it can either reinforce or attenuate the manifestation of SOs, depending on the phase of delivery. Importantly, CLAS effects have been shown to be primarily stimulus-locked and self-limited: phase-locked auditory clicks transiently amplify the targeted SO, but do not induce sustained modulation beyond the directly stimulated oscillatory cycles (Ngo et al., 2013; Ngo et al., 2015).

Across sleep studies, *in-phase* CLAS has been shown to modulate slow oscillatory activity and, in several cases, enhance sleep quality and declarative memory consolidation (Diep et al., 2021; Ngo et al., 2013; Ngo et al., 2015; Ong et al., 2016; Papalambros et al., 2017). However, other studies have reported no significant effects on memory outcomes (Henin et al., 2019; Ong et al., 2018), suggesting that the cognitive benefits of CLAS may depend on task type, stimulation parameters, and individual responsiveness. In a multi-night paradigm, repeated CLAS was associated with improvements in sleep continuity and memory performance, and with stimulation-response–dependent associations with plasma amyloid biomarkers (Aβ42/Aβ40 ratio), suggesting that sustained SW reinforcement can engage sleep-dependent physiological processes beyond acute EEG modulation (Zeller et al., 2024).

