The effectiveness of this technique relies on the intact transmission of auditory signals through the peripheral and central auditory pathways, beginning with cochlear activation and propagation via the vestibulocochlear nerve (cranial nerve VIII) to higher-order cortical regions (Bellesi et al., 2014; Esfahani et al., 2023; Ngo et al., 2013). Studies suggest that these signals ascend predominantly through the non-lemniscal pathway and reach higher-order associative regions, where they evoke event-related potentials in response to sound (Atienza et al., 2001; Hu, 2003; Jourde et al., 2023). Previous EEG and fMRI studies have confirmed that the brain retains its ability to process auditory stimuli during deep states of anesthesia (Hartikainen and Rorarius, 1999; Nourski et al., 2017; Plourde et al., 2006). These findings suggest that the necessary sensory and cortical pathways required for CLAS remain functional under anesthesia, providing a neurophysiological basis for exploring whether CLAS can effectively modulate anesthetized brain states.

Auditory stimulation is particularly well suited for closed-loop modulation of SOs under anesthesia for several reasons: auditory stimulation at low intensity offers a simple, non-invasive, and temporally precise approach for engaging slow oscillatory dynamics, with minimal interference with the surgical field. In sleep, auditory stimuli are well known to evoke K-complex–like responses that share core morphological and generative features with SOs and rely on corticothalamic circuitry involved in *δ*-wave generation (Cash et al., 2009; Colrain, 2005). Under propofol anesthesia, early auditory cortical responses and thalamocortical relay activity are suppressed but not abolished, providing a preserved pathway through which phase-locked auditory input may interact with drug-stabilized δ oscillations. This preserved auditory–corticothalamic coupling provides a mechanistic rationale for using auditory stimulation, rather than other sensory modalities, to probe and modulate slow oscillatory activity under general anesthesia (Ngo et al., 2013; Nourski et al., 2017).

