#### CLAS algorithm development

2.1.3

Our team has designed a CLAS algorithm for the real-time detection of *δ*-waves, which is directly integrated into an hd-EEG system (128-channel MagstimEGI), using custom Python scripts (Python 3.12.0). Online detection uses a single frontal channel (Fz) sampled at 500 Hz and filtered with a low-pass FIR filter plus moving average to achieve low-latency triggering (20 ms delay). Fz was selected to replicate established CLAS paradigms in sleep (Diep et al., 2021; Dudysová et al., 2024; Navarrete et al., 2020; Ngo et al., 2013; Ong et al., 2016; Papalambros et al., 2017) and because slow oscillations under propofol anesthesia exhibit frontal predominance and preferential involvement of medial cortical regions, with origins and propagation patterns aligned along mesial components of the default mode network (Murphy et al., 2011). For algorithm development and real-time visualization, the CLAS software simultaneously logs 20 additional channels (1–20). Simultaneously, NetStation software (MagstimEGI) acquires the full 128-channel raw EEG for offline analyses.

The CLAS software will deliver one of three types of stimulation: *in-phase*, in the up-slope or up-state of the δ-waves, aiming to be phase-locked with the peak of the δ-waves, *anti-phase*, in the down-slope or down-state of the δ-waves, aiming to be phase-locked with the trough of the δ-waves, and *sham*, where no stimulation happens, as a baseline.

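### Zero-crossing detection on continuous EEG cannot ensure that CLAS effects are endogenous, and contrasts with a silent sham mix phase-locking with the presence of sound

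*Protocol article*

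**What the plan says.** Section 3.2 of the protocol article describes two things.

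- **An evoked-response step.** EEG is averaged around sound onset, and "the corresponding average from the *sham* condition will be subtracted to isolate stimulus-evoked responses". Its stated use is to identify early auditory components.
- **The primary wave analysis.** Here "primary analyses of δ-wave dynamics are based on individually detected δ-waves defined independently of stimulus-locked averaging". The metrics listed (amplitude, slope, transition frequency, density) "are computed on continuous EEG signals using zero-crossing based criteria". From this the section concludes that the method is "ensuring that reported CLAS effects reflect modulation of endogenous oscillatory activity rather than purely evoked auditory responses".

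Other sections bear on that conclusion.

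- Section 1.5 says that in sleep "auditory stimuli are well known to evoke K-complex–like responses that share core morphological and generative features with SOs". It adds that under propofol early auditory responses are suppressed but not abolished. It also says that, in sleep, phase-locked clicks "do not induce sustained modulation beyond the directly stimulated oscillatory cycles".
- Section 2.1.3 defines sham as the condition "where no stimulation happens, as a baseline".
- Section 1.8 (SA1) and section 4.1 (H1) state the expected effects of in-phase and anti-phase stimulation against sham.
- The Figure 4 legend and section 3.7.1 define an offline wave by three consecutive zero-crossings and a duration of 250 to 10,000 ms. Section 3.7.1 compares all three conditions and includes PSD among the metrics.

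**The concern.** Independence from stimulus-locked averaging is not independence from the sound. No described step removes evoked activity from the signal before waves are detected and measured. The separation step produces an averaged evoked response, and nothing says that it corrects the wave metrics.

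If a sound adds a slow deflection to an unchanged background, the detector measures the sum. It may count an extra wave, split or merge existing ones, or report a different amplitude or slope. Restricting attention to some other stretch of the block does not help, because the effect of CLAS is expected only in the stimulated cycles, and those cycles carry the evoked response.

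The interpretation of SA1 is at stake. A difference between in-phase and sham could be modulation of ongoing δ activity, a superimposed evoked wave, or both. The same holds for anti-phase versus sham, where an evoked wave could also hide a true reduction.

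**Working it through.** The documents contain no figure to reproduce. The check is a reading of the sections together, followed by an illustration.

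**1. What a contrast with sham measures.** Write the recorded signal in a stimulated block as V = B + E, where B is the ongoing activity and E the summed evoked responses. In sham, V = B. For any metric M, the contrast is M(B + E) − M(B). With B unchanged by stimulation, this is not zero in general, whether or not M uses zero-crossings.

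**2. PSD.** P(V) = P(B) + P(E) + 2·Re S(B,E), where S(B,E) is the cross-spectrum. The detector does not enter. With randomly timed sounds the cross-term would average out. With phase-locked sounds it need not, and its sign depends on the phase targeted. The same formula shows why in-phase versus anti-phase is only a partial control. P(E) cancels only if the number of sounds and the evoked response are alike in both blocks, and the cross-terms do not cancel.

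**3. Can an evoked wave pass the offline criteria?** Offline, a wave needs zero-crossings and 250 to 10,000 ms. Nothing excludes a slow deflection that follows a sound.

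**4. Illustration with zero true modulation.** From the protocol: 30 subjects, one 180 s block per condition, triggering by the −40 μV, 0 μV and 75 μV rules (mirrored for anti-phase), and offline detection by zero-crossings and duration. The 500–2,000 ms condition was only approximated, by a 2 s upper limit. Assumed: background noise mainly at 0.4–1.5 Hz (SD 40 μV) plus 0.1–4 Hz noise (SD 10 μV), and an added waveform a·[−exp(−(t−0.5)²/(2·0.12²)) + 0.7·exp(−(t−0.9)²/(2·0.18²))], with t in seconds after the sound.

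Means with no offline amplitude threshold, given as in-phase / anti-phase / sham:

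| a (μV) | Density (/s) | Amplitude (μV) | Slope between extrema (μV/s) |
|---|---|---|---|
| 0 | 1.074 / 1.072 / 1.081 | 100.4 / 101.4 / 100.4 | 232.6 / 234.8 / 233.3 |
| 10 | 1.101 / 1.049 / 1.081 | 100.0 / 102.3 / 100.4 | 236.6 / 232.1 / 233.3 |
| 20 | 1.123 / 1.023 / 1.081 | 101.1 / 104.5 / 100.4 | 242.0 / 231.7 / 233.3 |
| 40 | 1.179 / 0.980 / 1.081 | 105.4 / 112.1 / 100.4 | 260.0 / 243.1 / 233.3 |

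- In-phase versus sham, paired t for density: −0.9 at 0 μV, 3.4 at 10 μV, 6.7 at 20 μV, 15.5 at 40 μV.
- At 40 μV, in-phase density rose by (1.179 − 1.081)/1.081 = 9.1%, slope by (260.0 − 233.3)/233.3 = 11.4% and amplitude by (105.4 − 100.4)/100.4 = 5.0%. These are the predicted directions. Duration fell from 0.914 to 0.840 s, which is against the prediction.
- At 40 μV, anti-phase amplitude rose by (112.1 − 100.4)/100.4 = 11.7%, against the predicted reduction, and density fell by (1.081 − 0.980)/1.081 = 9.3%.
- In-phase minus anti-phase at 40 μV: density 1.179 − 0.980 = 0.199/s, amplitude 105.4 − 112.1 = −6.7 μV. Both are non-zero with no modulation at all.
- Sounds delivered per block at 40 μV: 133 in-phase, 116 anti-phase.

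**5. How stable is this?** Not very. Adding an offline 75 μV threshold changed the in-phase density rise at 40 μV to (0.837 − 0.719)/0.719 = 16.4%. Other runs of an additive model with different backgrounds gave in-phase density changes between −7% and +0.2% when no offline threshold was used. With an offline threshold, a 50 μV wave and no 500–2,000 ms window they gave +28% to +47%, with anti-phase density rising by 18% to 38% rather than falling.

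**The case against.** The case for the plan has five parts.

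- **Sleep is not propofol.** The K-complex resemblance is stated for sleep. This stands: evoked waves *can* meet the offline criteria, and a reader who infers that they *do* so under propofol goes beyond the documents.
- **The text says purely evoked.** It does not deny a mixed effect. True, but the illustrated effect was purely evoked and still passed the detector, so the assurance fails even as worded.
- **Anti-phase is a sound-matched comparator.** It is in the three-condition comparison, and H1 predicts opposite directions, so a common rise in both sound blocks would count against H1. This stands in part. The contrast is not named as the test of phase specificity, and additive waves did not act alike at the two phases.
- **Evoked responses are part of the proposed mechanism.** Section 1.7 says that sounds evoke time-locked responses that engage δ-generating circuitry. This stands. It argues against subtracting the evoked residual or masking the post-sound window as a main correction, since either would also remove genuine stimulus-locked enhancement.
- **Sham markers may simply be condensed out.** The sham average in section 3.2 presupposes some time reference, and the full protocol may describe it. A reader might count the missing detail as an error; the article does not support that.

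**Conclusion.** The point holds as a matter of what the design can show. Section 3.2 asserts a property that zero-crossing detection on unprocessed continuous EEG does not have, and PSD lies outside the stated safeguard altogether. Both SA1 contrasts with sham mix phase-locking with the presence of sound.

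The size of any resulting bias under propofol cannot be derived from the documents. The illustration shows only that a bias is possible without any endogenous change. Its figures rest on an assumed background, waveform and evoked size, and they vary in magnitude and sign. A reader might infer that a positive SA1 result would be an artefact, or that one of the percentages above estimates the bias. Neither is supported. In-phase versus anti-phase is a necessary check on a phase-specific claim, but it does not by itself separate superposition from modulation.

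**What to change.** 1. In section 3.2, replace the assurance with a statement that contrasts with sham show the effect of phase-locked sound, including any evoked component, and that this applies to PSD as well as to the detected-wave metrics.
2. Name the within-subject in-phase versus anti-phase contrast, already available in the section 3.7.1 comparison, as a required test for any phase-specific claim. State that it is necessary but not sufficient, because evoked waves add differently at different phases.
3. Report the number of sounds delivered per block.
4. Optionally, and as a sensitivity analysis only, place virtual markers in sham by offline replay of Fz, and exclude or model waves in a matched window after each marker in all three blocks. State that this also removes the targeted cycles and is therefore biased towards no effect.

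Cost: one extra contrast, a count from the stimulation log, revised wording and a more cautious claim. No further patients or recording time are needed. The optional analysis adds one offline pass.

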### δ-waves metrics

3.3

Figure 4 illustrates some of the different metrics that are described in the following section. *Amplitude (μV):* The peak-to-peak amplitude was calculated as the absolute difference between the maximum and minimum values of the oscillation: 
$A_{e1-e2}=|V_{e1}-V_{e2}|$
, where *V_e1_* is the value of the first extremum in μV, and *V_e2_* is the value of the second extremum in μV. *Frequency (Hz)*: The mean frequency of the oscillation was defined as the inverse of its duration: 
$F=\frac{1}{d}$
. *Slopes (μV/s)*: We calculated three slope measures to quantify the rate of voltage change within each oscillation: (1) 1st zero-crossing to 1st extremum: 
$\text{slop}e_{\mathrm{zc}[i]\_e1}=\frac{|V_{e1}|}{t_{e1}}$
, (2) 1st extremum to 2nd extremum: 
$\text{slop}e_{e1\_e2}=\frac{A_{p-p}}{|t_{e1}-t_{e2}|}$
, (3) 2nd extremum to last zero-crossing: 
$\text{slop}e_{e2\_\mathrm{zc}[i+1]}=\frac{|V_{e2}|}{d-t_{e2}}$
, where *t_e1_* and *t_e2_* are the time (in seconds, relative to the initial zero-crossing) at which the first and second extremum occur, respectively. *Transition Frequency (Hz):* The transition frequency was defined as the inverse of twice the interval between the first extremum and the second extremum: 
$F_{\text{trans}}=\frac{1}{2|t_{e2}-t_{e1}|}$
. *Density (SOs/s)*: The density of delta waves (*δ*-waves) was defined as the number of δ-waves per second over the full duration of the recording: 
$\text{Density}=\frac{N_{\mathrm{\delta W}}}{T}$
, where *N_δW_* is the total amount of δ-waves detected in the recording, and *T* is the total duration of the recording in seconds.

**Figure 4 fig4:**
[figure not shown]
Delta-wave metrics. Quantification of δ-wave morphology. Each δ-wave is defined between three consecutive zero-crossings. Metrics include amplitude (difference between extremums, V_e1_–V_e2_), duration (time between first and last zero-crossings), slopes (rate of voltage change across segments), and transition frequency (inverse of twice the interval between extremums). These features provide sensitive markers of oscillatory dynamics under anesthesia and CLAS modulation.

### Functional analysis

3.4

Beyond univariate analyses, we will characterize the large-scale neural dynamics underlying depth of anesthesia by constructing functional connectivity networks for each stimulation block. Connectivity will be computed using weighted phase lag index (wPLI) (Vinck et al., 2011), where EEG data will first be filtered into canonical frequency bands (delta 1–4 Hz, theta 4–8 Hz, alpha 8–14 Hz, beta 14–30 Hz).

The wPLI isdefined as: 
$\mathrm{wPL}I_{\mathrm{ij}}=\frac{E\{ℑ(C_{\mathrm{ij}})\}}{E\{|ℑ(C_{\mathrm{ij}})|\}}=\frac{E\{|ℑ(C_{\mathrm{ij}})|\mathrm{sgn}(ℑ(C_{\mathrm{ij}}))\}}{E\{|ℑ(C_{\mathrm{ij}})|\}}$
,

where 
$ℑ(C_{\mathrm{ij}})$
 is the imaginary part of cross-spectrum the imaginary component of the cross-spectrum between signals *i* and *j*. The cross-spectrum is defined as C_ij_ = Z_i_Z_j_, with Z_i_ and Z_j_ denoting the Fourier spectrum of channel *i* and the conjugate spectrum of channel *j*. The wPLI values range from 0 (no consistent lag/lead relationship) to 1 (perfect non-zero phase locking) (Vinck et al., 2011).

To assess the directionality of functional connectivity, we will compute the directed phase lag index (dPLI) (Stam and Van Straaten, 2012). The instantaneous phase of each EEG channel will be extracted using a Hilbert transform. For each time point *t*, the phase difference between channels *i* and *j* will be computed as 
$\Delta \phi_{t}=\phi_{i,t}-\phi_{j,t}$
.

The dPLI is then given by: 
$\mathrm{dPL}I_{\mathrm{ij}}=\langle H(\Delta_{\mathrm{\varphi t}})\rangle$
,

where *H(x)* is the Heavyside step function: 
H(x)=1ifx>0,H(x)=0.5ifx=0,andH(x)=0
 otherwise. dPLI values >0.5 indicate that channel *i* consistently leads channels *j*, whereas values <0.5 indicates the opposite.

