### From sleep to anesthesia: a shared neurophysiological landscape

1.1

General anesthesia (GA) is often colloquially described as “falling asleep.” Although sleep and anesthesia arise from distinct mechanisms, they share striking neurophysiological signatures. Both are associated with a reversible loss of awareness, diminished sensory processing, and unresponsiveness to external stimuli (Brown et al., 2010; Murphy et al., 2011; Purdon et al., 2013). A central commonality is the presence of synchronized low-frequency activity in the electroencephalogram (EEG), most prominently within the delta frequency range (0.1–4 Hz) (Massimini et al., 2004; Steriade et al., 1993). This convergence has motivated extensive comparisons between anesthesia, sleep, and coma in the neuroscience of consciousness (Akeju and Brown, 2017; Bonhomme et al., 2016; Boveroux et al., 2010; Mashour, 2024; Mashour and Hudetz, 2018).

Within the delta band, two related but distinct phenomena can be identified: slow oscillations (SOs; <1 Hz) and slow waves (SWs; 1–4 Hz) (Massimini et al., 2004; Steriade et al., 1993). SOs are large-amplitude, <1 Hz oscillations representing the alternation between cortical up- and down-states, and are considered the fundamental rhythm of deep non-rapid eye movement (NREM) sleep (Sanchez-Vives and McCormick, 2000; Steriade et al., 1993a, 1993b). In contrast, SWs are faster oscillations in the delta band that often co-occur with SOs but may involve partially distinct synchronization mechanisms, especially thalamocortical contributions (Timofeev and Chauvette, 2011). Together, SOs and SWs form the backbone of the EEG slow-wave activity (SWA) that typifies both deep sleep and anesthesia. For clarity, in the remainder of this manuscript we will use the term “*δ*-waves” to collectively refer to SOs and SWs, unless explicitly distinguished. Here we adopt a slightly broadened delta range (0.1–4 Hz) to encompass very slow fluctuations approaching the classical SO band.

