### EEG pre-processing

3.1

EEG data will be preprocessed using a custom MNE Python script and will be bandpass filtered from 0.1 to 50 Hz. Non-scalp, noisy channels, and channels overlapping with the BIS monitor will be removed. EEG data will be re-referenced to an average reference. Data will then be segmented into the 6 conditions of study: (1) *In-phase*; (2) *Anti-phase*; (3) *sham*; (4) *Pre-Pain*; (5) *Pain*; (6) *Post-Pain*.

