### Graph theoretical properties

3.5

For each frequency band, wPLI matrices will be thresholded into adjacency matrices, and graph-theoretical analyses will be performed. Core measures will include global efficiency (Latora and Marchiori, 2001), clustering coefficient (Watts and Strogatz, 1998), modularity (Newman, 2006), and small-worldness (Humphries and Gurney, 2008). Network hubs will be identified using node degree and betweenness centrality, reflecting the integration role of highly connected nodes (Van Den Heuvel and Sporns, 2013). Particular focus will be given to frontoparietal connectivity, which is strongly implicated in anesthetic-induced unconsciousness (Lee et al., 2013).

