#### Effect of CLAS on *δ*-waves morphology and topography

3.7.1

EEG data will be processed at the level of individual channels to characterize the impact of CLAS on δ-wave morphology and topography using custom Python scripts. Each detected δ-wave will be segmented as a single event (250–10,000 ms duration), and morphology will be quantified by amplitude, slope, transition frequency, density, and power spectral density (Bouchard et al., 2021). These metrics will be compared across conditions (*in-phase*, *anti-phase, sham*) and cortical regions of interest (frontal, central, midline, parietal, temporal, occipital). Descriptive statistics will be computed at both the subject and group level, with comparisons assessed using repeated-measures ANOVA and independent-samples *t*-tests, including age and sex as covariates.

Topographical EEG maps will be generated for canonical frequency bands (delta (0.1–4 Hz), theta (4–8 Hz), alpha (8–13 Hz), beta (13–30 Hz)), and phase-amplitude coupling measures will be calculated to further assess condition-dependent differences in oscillatory dynamics. Topographical mapping will allow testing for regional differences, as frontal predominance of *δ*-waves is a hallmark of both sleep and propofol anesthesia (Murphy et al., 2011; Purdon et al., 2015). To extend beyond scalp measures and as an exploratory aim, source estimation will be performed using standardized head models (Michel and He, 2019). Finally, propagation analyses will be conducted to quantify directionality of δ-wave travel across the cortex, as slow oscillations are known to spread as traveling waves and have been proposed as indices of large-scale cortical communication (Massimini et al., 2004; Tononi and Massimini, 2008).

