### Primary hypothesis (H1): phase-specific modulation of SWA by CLAS

4.1

We anticipate phase-specific effects of CLAS on *δ*-wave dynamics during propofol anesthesia. *In-phase* CLAS should enhance δ-wave morphology and power relative to *sham*, increasing peak-to-peak amplitude, steepening slopes between extrema, prolonging, and augmenting PSD in 0.1–4 Hz, consistent with sleep (Ngo et al., 2013; Ngo et al., 2015; Zeller et al., 2024). *Anti-phase* CLAS is expected to disrupt *δ*-wave expression (reduced amplitude, flatter slopes, shorter duration, lower PSD), reflecting the directional nature of phase-locking (Esfahani et al., 2023). Topographically, frontal predominance is expected for *in-phase* CLAS effects (Murphy et al., 2011; Purdon et al., 2015), and source/propagation analyses should implicate prefrontal-cingulate generators and anterior to posterior traveling waves typical of unconscious states (Massimini et al., 2004).

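### Connectivity and graph analyses filter delta at 1–4 Hz with no band below 1 Hz, although the protocol defines delta as 0.1–4 Hz and triggers stimulation on waves of about 0.25–1 Hz

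*Protocol article*

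**What the plan says.** Section 1.1 separates "slow oscillations (SOs; <1 Hz) and slow waves (SWs; 1–4 Hz" and then merges them into one study-wide range: "Here we adopt a slightly broadened delta range (0.1–4 Hz) to encompass very slow fluctuations approaching the classical SO band". Section 1.5 says the two components are handled together and that stimulation is aimed at the whole 0.1–4 Hz range; the primary objective in section 1.8 uses that range too. Pre-processing keeps the low end, since the data "will be bandpass filtered from 0.1 to 50 Hz" (section 3.1). Section 3.7.1 maps topography in "canonical frequency bands (delta (0.1–4 Hz), theta (4–8 Hz), alpha (8–13 Hz), beta (13–30 Hz", and section 4.1 predicts "augmenting PSD in 0.1–4 Hz".

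Section 3.4 differs. It computes wPLI in "canonical frequency bands (delta 1–4 Hz, theta 4–8 Hz, alpha 8–14 Hz, beta 14–30 Hz". Section 3.5 carries this forward: "For each frequency band, wPLI matrices will be thresholded into adjacency matrices". Neither section lists a band below 1 Hz or gives a reason for the narrower delta. Section 3.4 also says of wPLI: "The wPLI values range from 0 (no consistent lag/lead relationship) to 1 (perfect non-zero phase locking".

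**The concern.** The article fixes two delta bands and calls both sets of bands canonical. The narrower one is exactly the range that section 1.1 assigns to slow waves, so section 3.4 separates slow oscillations from slow waves and drops the former, although section 1.5 says they are not separated.

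The consequence falls on Specific Aim 2. Section 4.4 predicts more locally coherent delta-band activity during in-phase stimulation and presents the network analysis as a test of whether stronger delta waves fragment the network further. If the strengthened waves lie mostly below the analysed band, a null delta-band result could mean no network effect or a filter that removed the relevant signal, and the design could not tell these apart. Leaving two bands in the plan also leaves the choice open until the data are in hand.

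**Working it through.** **Reproducing the 0.1–4 Hz range.** Section 3.3 defines wave frequency as F = 1/d. Section 3.7.1 admits offline events of 250–10,000 ms.
- 1/10 s = 0.1 Hz
- 1/0.25 s = 4 Hz

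The offline event limits give 0.1–4 Hz exactly, so the wave metrics and the study-wide definition agree.

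**Range of the triggered waves.** Section 2.1.4 requires 500–2,000 ms between the two extrema for both in-phase and anti-phase detection. Section 3.3 defines transition frequency as F_trans = 1/(2|t_e2 − t_e1|).
- 1/(2 × 0.5 s) = 1.0 Hz
- 1/(2 × 2.0 s) = 0.25 Hz

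The triggered range is 0.25–1.0 Hz on this measure. Its overlap with 1–4 Hz is the single point 1.0 Hz.

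**Whole-wave frequency.** A wave spans more than the interval between its extrema, so d > 0.5 s and F < 1/0.5 = 2 Hz. An asymmetric qualifying wave can therefore lie between 1 and 2 Hz on F = 1/d.

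**Share of the defined band left out.** 0.1–1 Hz is 0.9/3.9 = 23% of 0.1–4 Hz on a linear scale and ln(10)/ln(40) = 62% on a log scale.

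**What a 1–4 Hz filter passes.** The article gives no filter design, so two designs were assumed to show the range of power passed:
- Zero-phase 4th-order Butterworth: about 0% at 0.5 Hz, 0.1% at 0.75 Hz, 25% at 1.0 Hz.
- FIR with a 1 Hz-wide transition: about 2% at 0.25 Hz, 25% at 0.5 Hz, 77% at 0.75 Hz, 99% at 1.0 Hz.

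The loss runs from near-total to partial, depending on the design.

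**Cycles available below 1 Hz** (frequency × duration).
- 180-s block: 0.25 × 180 = 45; 0.1 × 180 = 18.
- 30-s Pain epoch: 0.25 × 30 = 7.5; 0.1 × 30 = 3.

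**The wPLI formula.** Both printed forms are E{Im(C)}/E{|Im(C)|}, because |x|·sgn(x) = x. Exchanging channels i and j conjugates the cross-spectrum and flips the sign of its imaginary part. The printed quantity therefore runs from −1 to 1 and is antisymmetric, against the 0–1 range stated beside it.

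**The case against.** The trigger rule limits which waves start a sound; it does not limit where the effect appears. Asymmetric waves can reach almost 2 Hz, non-sinusoidal waves have harmonics above 1 Hz, section 4.1 predicts steeper slopes, and a gentle filter leaves part of the sub-1 Hz signal in place. This stands. A reader might infer that connectivity is tested in a band the stimulation does not touch, or that a null would carry no information; the documents support neither.

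The reach is also limited. Specific Aim 2 names no band for its frontoparietal and integration predictions, and in section 4.4 only local coherence is tied explicitly to delta. Three other bands are analysed. Per-block connectivity can still be related to the 0.1–4 Hz wave results although the bands differ. The band sentence is attached to wPLI, so dPLI has no stated band rather than a wrong one. All of this stands.

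On the formula, the stated 0–1 range makes the intent clear. A reader might infer that thresholding would lose about half the channel pairs. That happens only if one triangle of the signed matrix is thresholded: in the full antisymmetric matrix every non-zero pair has one positive entry. The article does not say which is used.

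Finally, a single 0.1–4 Hz band spans 40:1, and phase-lag measures over so wide a band are hard to interpret. Simply widening delta in section 3.4 is therefore debatable. What the objection does not supply is a reason in the text for 1–4 Hz.

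**Conclusion.** The inconsistency is real and should be fixed. Section 3.4 alone uses 1–4 Hz, nothing below 1 Hz enters the wPLI or graph analyses as a band, and the triggered range of 0.25–1.0 Hz touches the analysed delta band only at its edge. The delta-band network result would come mostly from outside the range of the triggered waves, and a null there would be hard to interpret. This rests on using transition frequency to describe the triggered waves; the exact signal loss depends on a filter design the article does not give.

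Connectivity and graph measures are secondary outcomes. The delta limit does not affect theta, alpha or beta connectivity, BIS, microstates, or the primary morphology, density and power analyses. The missing modulus and the 13 versus 14 Hz alpha/beta edge are minor corrections.

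**What to change.** In section 3.4, add a separate pre-specified band below 1 Hz that covers the triggered range, for example 0.25–1 Hz, beside 1–4 Hz. Carry it into the graph measures of section 3.5, and state the band or bands for dPLI. Alternatively, keep 1–4 Hz alone, give the reason, and limit the delta network claims in section 4.4 to slow waves.

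In the same edit, write wPLI as |E{Im(C)}| / E{|Im(C)|}, and use one alpha/beta edge in sections 3.4 and 3.7.1.

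The cost is a filter setting, one formula and a few sentences, with no new data. The price is precision: few cycles at the lowest frequencies, equal across the three 3-minute blocks but severe in the 30-s Pain epoch if connectivity is computed there, and one more band in the multiplicity correction.
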